## Background

There is a high rate of psychological comorbidity in people with alcohol dependence [1,2]. This is of concern given that, during treatment, the time to relapse is shorter, the drop-out rate is increased, and long-term alcohol consumption is greater for those with comorbid major depression or anxiety disorder than for those with an alcohol use disorder (AUD) with no comorbid mental disorder [3-5]. In the Australian National Survey of Mental Health and Wellbeing, Teesson and colleagues [6] reported that 33% of more than 10,000 respondents with an AUD also suffered from an anxiety or mood disorder as defined by the *Diagnostic and Statistical Manual of Mental Health Disorders,* 4th ed. (DSM-IV). In addition, this subpopulation was significantly more disabled and used health services more frequently than those with AUD with no comorbid mental disorder [6]. Results from the large alcohol treatment trial Project MATCH (Matching Alcohol Treatment to Client Heterogeneity) highlight psychiatric comorbidity as a significant factor influencing treatment response for alcohol dependence [7]. Similarly, we have reported that, among alcohol-dependent patients, clinically significant levels of depression predicted poor response to alcohol treatment [8]. Unfortunately, however, the treatment of alcohol dependence and psychological disorders is often the responsibility of different services, and this may hinder the treatment process. Accordingly, there is a need for an effective integrated treatment for alcohol dependence and comorbid anxiety or depression in outpatient services.

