### Participants

A total of 100 patients will be recruited from inpatients and outpatients of participating hospitals via flyers and community advertisements at local general practice offices, in newspapers, and on the Sydney Alcohol Treatment Group website. Conservatively assuming that 40% of respondents will not be eligible for randomization at step 2 following diagnosis for depression or anxiety disorder, we anticipate that 60 patients will be randomized to one of the two groups. Participant time and travel expenses will be reimbursed at follow-up assessments. The trial will be conducted at the Drug Health Services outpatient clinic of the Royal Prince Alfred Hospital, NSW, Australia. Ethics approval for the study has been granted by The Sydney Local Health District Ethics Review Committee (X05-0275).

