### Statistical analysis

The modified intention-to-treat principle will be used such that all subjects who attend the first intervention session will be analyzed [50]. The success of randomization will be tested by comparing baseline characteristics of the study groups with potentially confounding variables included as covariables. Analysis of variance will be used to compare continuous variables. Categorical variables will be compared via chi-square test. The effect of treatment on time-related outcome measures such as lapse and relapse will be analyzed by life-table survival analysis. Binary linear generalized estimating equations (GEE), with autoregressive correlation matrices, will be employed to determine differences between integrated care and usual care groups on change in anxiety or mood symptoms. A series of regression analyses will be performed to assess the role of symptomatic change in alcohol consumption and vice versa. Last-point carried forward or multiple imputation will be used to determine the scores of participants who drop out or are lost to follow-up. One previous study [9] with a similar design (N = 35) demonstrated that combined CBT treatment of alcohol dependence and comorbid depression significantly improved alcohol use outcomes with a moderate effect size. Power analysis has thus been performed such that a sample of 60 subjects (30 per group) has 80% power of detecting a moderate difference between the two arms of care on alcohol use outcomes at alpha = 0.05.

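### The stated 80% power for a moderate difference cannot be reproduced at a conventional moderate effect: with 30 analysed per group it needs about 0.74 SD two-sided, or a hazard ratio of about 0.49 with 60 events

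*Protocol article*

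**What the plan says.** The power statement is in the Statistical analysis section of the protocol article. An earlier trial of 35 patients is reported to have "significantly improved alcohol use outcomes with a moderate effect size". The article builds its own claim on this: "a sample of 60 subjects (30 per group) has 80% power of detecting a moderate difference between the two arms of care". The claim is made for the alcohol outcomes, with alpha set at 0.05. No standardized difference, SD, proportion, hazard ratio, event count or sidedness is given.

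The Outcome measures section lists time to lapse, time to relapse, total abstinence and average consumption per drinking day as primary outcomes. The Statistical analysis section names analysis of variance for continuous variables, chi-square for categorical variables and life-table survival analysis for the time outcomes. Generalized estimating equations are assigned to anxiety or mood symptoms.

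On numbers, the Participants section says "we anticipate that 60 patients will be randomized to one of the two groups", after 40% of 100 recruits prove ineligible. The analysis set is narrower: "all subjects who attend the first intervention session will be analyzed".

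**The concern.** The sentence gives a sample size, an alpha and a power, and describes the effect in one word. A reader will supply the usual meaning of that word, about half a standard deviation. On that meaning, 30 per group is known to fall well short of 80%.

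What is at stake is how the result will be read. The Discussion section concedes possible lack of power only for processes and mechanisms, so the main comparison will be taken as adequately powered. If the true benefit is 0.5 SD, a two-sided test would miss it about half the time. A null result could then be read as evidence against integrated care from a design that could not reliably detect such a benefit.

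**Working it through.** **Inputs from the protocol article:** 30 per group, alpha 0.05, stated power 80%.

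**Assumptions, because the article gives no figure:** moderate means d = 0.5 for a two-group mean difference (equivalently f = 0.25 in a two-group analysis of variance) or w = 0.3 for chi-square. Two-sided is the main case and one-sided is also shown.

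**1. Attempt to reproduce the 80%, continuous outcome.** The two-group analysis of variance is a t-test with 58 degrees of freedom and noncentrality d × √(n/2) = 0.5 × √15 = 1.936.
- Two-sided critical value 2.002: power 47.8%.
- One-sided critical value 1.672: power 60.6%.

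**2. Attempt to reproduce it, categorical outcome.** Chi-square with 1 degree of freedom has noncentrality N × w² = 60 × 0.09 = 5.4. Power is 64.2%.

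None of these is close to 80%. At d = 0.5, 80% power two-sided needs 63.8, so 64 per group or 128 in total. That is about twice the planned size.

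**3. What 30 analysed per group can detect with 80% power.** Solving the same t-test for d:

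| Sidedness | Detectable difference |
|---|---|
| Two-sided | 0.736 SD |
| One-sided | 0.650 SD |

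Intermediate two-sided values are 63% power at 0.6 SD and 76% at 0.7 SD. By the same convention a large difference is 0.8 SD, so 0.74 lies nearer to large than to moderate.

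**4. Time to lapse and time to relapse.** Power depends on the number of events D. With equal groups, Schoenfeld's formula gives the detectable hazard ratio as exp[−2 × (1.960 + 0.842)/√D].

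| Events | Hazard ratio, two-sided | Hazard ratio, one-sided |
|---|---|---|
| 60 (every patient) | 0.485 | 0.526 |
| 50 | 0.453 | 0.495 |
| 40 | 0.412 | 0.456 |

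The one-sided column uses 1.645 in place of 1.960. Freedman's formula gives 0.469 with 60 events, two-sided. The article states no event count, so the rows below 60 only illustrate the direction.

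**5. Analysed number.** Sixty is the forecast of patients randomized, and it is also the number in the power sentence. The analysis set drops anyone who misses the first session, so it can be 60 or fewer but not more. The article gives no rate for this, so no reduced power is asserted here.

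**The case against.** **The effect is undefined.** The decisive input, 0.5 SD, comes from convention and not from the article. If the authors meant about 0.74 SD two-sided or 0.65 SD one-sided, 80% follows. This stands. A reader might infer that the article contains a proven arithmetic error, but that would need a stated effect that fails to give the stated power.

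**The cited trial may imply a larger effect.** With 35 patients split 17 and 18, a simple two-group test is significant at two-sided 0.05 only if the observed d is at least 0.69; d = 0.5 would give p = 0.15. So the effect called moderate may have been near 0.69 SD. This has force, but it does not rescue the sentence. At d = 0.69, 30 per group give 75% power two-sided (84% one-sided). That trial may also have used an adjusted or repeated-measures analysis, and its numerical effect is not reported in the article.

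**Other models reach 80% at an effect labelled medium.**
- A one-predictor regression with f² = 0.15 gives 84%. As a two-arm contrast this is d = 2 × √0.15 = 0.775, again close to large. The article assigns regression to the links between symptom change and drinking.
- Baseline adjustment reaches 80% at d = 0.5 only with a baseline–outcome correlation of about 0.72, and no such correlation is stated.
- A group-by-time interaction at f = 0.25 gives about 90% or more at a within-subject correlation of 0.3 or higher. However, the repeated-measures model is assigned to anxiety or mood symptoms, and the power claim concerns alcohol outcomes.

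**A condensed article may leave the model to the full protocol or analysis plan.** That is fair for detail merely omitted. Here a definite power figure is printed, so it can be checked as it stands.

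**Loss to follow-up.** A reader might infer from the Background remark that "the drop-out rate is increased, and long-term alcohol consumption is greater" that a specific share of the 60 will be lost and power will fall to a specific lower value. The documents do not support a figure. The remark is general background, the 40% ineligibility assumption is described as conservative, and drop-outs' scores are to be imputed.

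**Conclusion.** The concern holds in a conditional form. At a conventional moderate effect, none of the tests the article names reaches 80% with 30 per group. Power is 48% two-sided or 61% one-sided at 0.5 SD, and 64% for w = 0.3. The 80% is right only for a difference of about 0.74 SD two-sided (0.65 SD one-sided). For the time outcomes it needs a hazard ratio of about 0.49 in the best case of 60 events. So the sentence either overstates power or applies the word moderate to an effect closer to large, and the article does not let the reader tell which.

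This rests on the conventional values for moderate, on 30 analysed per group, and on the analysis of variance and chi-square sentences applying to the alcohol outcomes as well as to baseline. If they cover baseline only, life-table analysis is the one method named for alcohol outcomes, and the hazard ratio result carries the point. Attrition, event counts below 60 and particular abstinence rates are not part of the conclusion.

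**What to change.** Keep 60 patients and replace the power sentence. The new text should:
- state the numerical effect, the test and outcome it refers to, and the sidedness behind the calculation;
- say that 30 analysed per group give 80% power for about 0.74 SD (two-sided alpha 0.05), or for a hazard ratio of about 0.49 with 60 events, and about 48% power for 0.5 SD;
- give the same figures at the sponsor's own expected number analysed after first-session losses, and at its own expected event count;
- note that a non-significant result would not exclude a moderate (0.5 SD) benefit.

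The cost is one paragraph of protocol or analysis-plan wording and a less favourable stated power. No extra patients are needed.

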## Discussion

The main aim of the current study is to assess the effectiveness of a CBT-integrated intervention for alcohol-dependent patients with comorbid anxiety and/or depression compared with usual care in reducing alcohol consumption and symptoms of anxiety and depression in an outpatient hospital setting. This study has several strengths, including a randomized controlled assessor-blind design that attempts to address a serious gap in the treatment evidence. However, one challenge may include generalizability of the results given the specialized integrated intervention.

In addition, the secondary aims of the study are to determine factors that mediate the relationship between treatment condition and drinking and/or mood outcomes and to describe important factors relating to the maintenance of alcohol-related psychiatric comorbidity. Targeting specific mechanisms that may underlie comorbidity during treatment is likely to be a productive strategy. However, a limitation of the current study may include the capacity to document these processes and mechanisms with adequate power.

The study findings will have potential implications for clinical practice by evaluating the implementation of specialized integrated treatment for comorbid anxiety and/or depression in an alcohol outpatient service. The results may, therefore, improve treatment outcomes for people with alcohol dependence by addressing fundamental barriers to treatment response. A clearer understanding of these issues is a prerequisite to devising and implementing appropriate clinical interventions.
